## Abstract

**Background:**

Bell’s palsy or acute idiopathic lower motor neurone facial paralysis is characterized by sudden onset paralysis or weakness of the muscles to one side of the face controlled by the facial nerve. While there is high level evidence in adults demonstrating an improvement in the rate of complete recovery of facial nerve function when treated with steroids compared with placebo, similar high level studies on the use of steroids in Bell’s palsy in children are not available. The aim of this study is to assess the utility of steroids in Bell’s palsy in children in a randomised placebo-controlled trial.

**Methods/Design:**

We are conducting a randomised, triple-blinded, placebo controlled trial of the use of prednisolone to improve recovery from Bell’s palsy at 1 month. Study sites are 10 hospitals within the Australian and New Zealand PREDICT (Paediatric Research in Emergency Departments International Collaborative) research network. 540 participants will be enrolled. To be eligible patients need to be aged 6 months to < 18 years and present within 72 hours of onset of clinician diagnosed Bell’s palsy to one of the participating hospital emergency departments. Patients will be excluded in case of current use of or contraindications to steroids or if there is an alternative diagnosis. Participants will receive either prednisolone 1 mg/kg/day to a maximum of 50 mg/day or taste matched placebo for 10 days. The primary outcome is complete recovery by House-Brackmann scale at 1 month. Secondary outcomes include assessment of recovery using the Sunnybrook scale, the emotional and functional wellbeing of the participants using the Pediatric Quality of Life Inventory and Child Health Utility 9D Scale, pain using Faces Pain Scale Revised or visual analogue scales, synkinesis using a synkinesis assessment questionnaire and health utilisation costs at 1, 3 and 6 months. Participants will be tracked to 12 months if not recovered earlier. Data analysis will be by intention to treat with primary outcome presented as differences in proportions and an odds ratio adjusted for site and age.

**Discussion:**

This large multicenter randomised trial will allow the definitive assessment of the efficacy of prednisolone compared with placebo in the treatment of Bell’s palsy in children.

**Trial registration:**

The study is registered with the Australian New Zealand Clinical Trials Registry ACTRN12615000563561 (1 June 2015).

## Background

Bell’s palsy, also known as acute idiopathic lower motor neurone facial paralysis, is characterized by sudden onset paralysis or weakness of the muscles to one side of the face controlled by the facial nerve. Bell’s palsy is an idiopathic, presumed immune mediated phenomenon, possibly with an infection as the inciting event [1–3]. In addition to the muscles of facial expression, the affected seventh cranial nerve in Bell’s palsy also supplies the taste buds to the anterior two thirds of the tongue, muscles associated with hearing, and the salivary and lacrimal glands. The early effect of Bell’s palsy is an inability to fully close the mouth and eye on the affected side of the face, causing difficulties in eating and speaking, corneal drying and erosion. Later symptoms can include pain around the ear sometimes extending to the back of head/neck, altered taste, synkinesis (involuntary facial movements), facial spasm, facial contracture, dysfunctional lacrimation (corneal drying and/or crocodile tears) and noise intolerance [2]. The resulting impairment of oral competence, verbal communication and social interaction, can contribute to significant emotional distress during Bell’s palsy [4–7].

Data from the United Kingdom reported an incidence of Bell’s palsy of more than 6 per 100,000 person-years in children under 14 years and more than 20 per 100,000 person-years in people aged 15–29 years [8], although the true incidence may be higher [9]. In an emergency department based study of stroke mimics in children [10] Bell’s palsy was the third most frequent diagnosis in children with sudden onset neurological dysfunction. In adults, up to 30 % of untreated patients fail to make a complete recovery [11]. While in children up to 100 % recover from Bell’s palsy within 12 months, it often leaves them with a prolonged period of functional impairment, disfigurement and emotional distress [4, 12–16].

The main agents used for the treatment of Bell’s palsy are steroids. The anti-inflammatory effect of steroids (such as prednisolone) is assumed to minimize facial nerve swelling, compression and damage, therefore reducing the length of time to and increasing the likelihood of recovery [2, 17]. Two recent, large, blinded randomised controlled trial (RCTs) of steroids in adults [18, 19] (combined *n* = 1309) reported statistically and clinically significant improvements in the proportion who reached complete recovery when Bell’s palsy was treated with steroids compared with placebo. The participants in both studies were randomised to receive prednisolone and acyclovir, prednisolone and placebo, acyclovir and placebo or placebo and placebo. One of the studies, by Engstrom et al. (839 patients), showed shorter times to recovery for patients who received prednisolone compared with those who did not (combining those who did and did not receive acyclovir, hazard ratio 1.4 95 % confidence interval [CI] 1.18 to 1.64; *p* < 0.0001) [19]. The other study (Sullivan et al., 496 patients) found that more patients had complete recovery by 3 months in the group who received prednisolone (83 %) compared with placebo (63 %) (again combining participants who did and did not receive acyclovir, difference 19.4 %; 95 % CI: 11.7 to 27.1 %); number needed to treat to achieve one additional complete recovery was 6 (95 % CI: 4 to 9) [18]. A recent (2010) Cochrane review (8 trials, *n* = 1569) on treatment for Bell’s palsy [17], including the two RCTs above, found that corticosteroid treated patients had a lower risk of incomplete recovery than placebo treated patients (relative risk [RR] 0.71; 95 % CI 0.61 to 0.83) and that those treated with corticosteroids also had reduced risk of synkinesis during follow up (RR 0.6; 95 % CI 0.44 to 0.81). Subsequently, in 2012 the *American Academy of Neurology* released a guideline update on the use of steroids and antivirals to treat Bell’s palsy [20]. It concluded that steroids have proven efficacy in treating Bell’s palsy in adults, and that no further research is required. Similarly, in 2013 the *American Academy of Otolaryngology-Head and Neck Surgery Foundation* published a clinical practice guideline recommending the use of oral steroids within 72 hours in patients with Bell’s palsy 16 years and older [21].

Despite the conclusive evidence of benefit from steroids in adults with Bell’s palsy, two systematic review of the use of steroids to treat Bell’s palsy in children found no placebo controlled trials [13, 22]. There has only been one small randomised trial of steroid use in children with Bell’s palsy. Unüvar et al. [12] randomised 42 children (mean age 53 months) to receive 1 mg/kg/day of methylprednisolone or no treatment (no placebo). The study found that all children fully recovered within 12 months regardless of treatment. However, at 4 and 6 months after treatment, more children in the methylprednisolone group had recovered compared with the no treatment group (86 vs 72 % at 4 months and 100 vs 85 % at 6 months). These findings suggest that although children eventually recover, steroids hasten the time to recovery. The lack of a placebo arm, small patient numbers, and inclusion of only children with severe signs and symptoms at presentation limit the generalisability of these results. Two systematic reviews of the use of steroids to treat Bell’s palsy in children found no placebo controlled trials and either state that there was insufficient evidence to make a treatment recommendation [13] or provide no positive evidence for the beneficial effects of corticosteroids and do not recommend the routine use of steroids in children [22]. The results from adult studies of steroids to treat Bell’s palsy are difficult to extrapolate to children as medical conditions often manifest differently and have different responses to treatment in adults and children. For example, there are documented differences from adults in the pathophysiology [23] and natural history of other paediatric demyelinating conditions: (i) acute disseminated encephalomyelitis, which is typically monophasic, has different presenting features and involves different brain structures than similar diseases in adults (such as multiple sclerosis) [24, 25]; (ii) acute myelitis can have a good prognosis in children but usually has a poor prognosis in adults [26]. Similarly, it is unclear whether the pathophysiology in children is different from adults.

Both systematic reviews of the use of steroids to treat Bell’s palsy in children [13, 22] call for a definitive trial to be conducted. The *American Academy of Neurology* similarly called for RCTs to determine if Bell’s palsy in children should be treated with steroids [20]. The *American Academy of Otolaryngology-Head and Neck Surgery Foundation* clinical practice guideline states that corticosteroids may be considered in pediatric patients with a large role for care giver involvement in the decision making process [21]. A consequence of the lack of evidence and firm treatment recommendations is variable use of steroid in children reported from a number of centers [4, 13, 14, 16].

Based on the lack of placebo-controlled evidence for or against steroid use in Bell’s palsy in children and the resulting variability in care, and the high level evidence of the efficacy of prednisolone in adults we designed a study with the primary aim to determine, in children aged between 6 months and less than 18 years presenting to the emergency department (ED) with symptoms of Bell’s palsy (unilateral, peripheral facial nerve palsy), whether treatment with oral prednisolone (at ~1 mg/kg daily for 10 days) increases the proportion of children who have complete recovery at 1 month (defined as grade 1 on the House-Brackmann (HB) scale [18, 27]) compared with children receiving placebo. This study will also provide a unique insight into Bell’s palsy related questions including the time to complete recovery; the emotional and functional impact of Bell’s palsy; the effect of initial severity and time to treatment on subsequent recovery; and the nature of pain, motor synkinesis and autonomic dysfunction in children with Bell’s palsy.

## Methods

### Study design

This is a phase III, triple-blinded, randomised, placebo-controlled superiority trial of prednisolone for treatment of Bell’s palsy. Participants will be randomised in a 1:1 ratio to receive ~ 1 mg/kg/day of prednisolone, up to a maximum of 50 mg, or matched placebo for 10 days. The study will include a total of 540 children (approximately 270 in each treatment group). This sample size allows for 10 % loss to follow-up at 1 month. The study will be conducted at sites of the Paediatric Research in Emergency Departments International Collaborative (PREDICT) research network in Australia and New Zealand [28]. The central study site is the Murdoch Childrens Research Institute in Melbourne (MCRI), Australia and the central study pharmacy is at the co-located Royal Children’s Hospital (RCH), Melbourne, Australia.

### Outcomes

#### Primary outcome

The primary outcome is complete recovery at 1 month post randomisation, where recovery is defined as a House Brackmann score of 1 [18, 27]. Recovery will be assessed face-to-face by a site specialist clinician who may be a pediatric neurologist, ear-nose-throat (ENT) specialist, pediatrician or ED physician. Where the participant is unable to attend the study site, it may be completed via videoconference using an online tool.

There are several different tools used in studies to describe the degree of facial dysfunction of Bell’s palsy, including the House Brackmann (HB) [12, 18, 19, 29–31], Sunnybrook [19, 32], Facial Paralysis Recovery Index/Profile [29, 33], and Yanagihara grading systems [34, 35]. The two largest adult RCTs used Sunnybrook scale and HB scale, or the HB scale alone [18, 19], and the only RCT of steroids for treating Bell’s palsy in children from Unüvar et al. [12] used the HB scale to assess recovery. In line with these studies, the primary tool to determine outcome in this study is the HB scale as used slightly modified by Sullivan et al. [36].

Using the HB scale, the two largest adult studies defined recovery as reaching a HB grade of 1 (HB 1) [18, 19]; others, including Unüvar [12], used HB grade 1 or 2. Sullivan et al. [18] initially set ‘complete recovery’ at HB grade 1 or 2, however, very early in the study the investigators found that participants only looked and felt fully recovered once HB grade 1 was obtained and hence changed their definition to HB grade 1. Our study accordingly defines full recovery as having achieved HB grade 1.

There are currently limited data regarding how long it takes children to recover from Bell’s palsy but existing data suggest a more rapid recovery in children than in adults [4, 12, 14, 37]. Unüvar’s study of 42 children [12] found that 72 % of children had complete recovery at four months, 85 % at six months, and 100 % recovery at 12 months without steroids. In two paediatric observational studies [4, 14], the mean time to recovery was five weeks (range 1–21 weeks) and 59 % had recovered at 1 month without steroids. Therefore the primary outcome in the current study was chosen as complete recovery at 1 month with recovery at 3 and 6 months as secondary outcomes.

#### Secondary outcomes

The secondary outcomes are:Complete recovery at 1 month using the Sunnybrook scale [32, 38]Complete recovery at 3 months using the Sunnybrook scaleComplete recovery at 3 months using the HB scaleComplete recovery at 6 months using the Sunnybrook scaleComplete recovery at 6 months using the HB scaleComplete recovery at 1, 3 and 6 months using the HB scale according to age, time to treatment and initial severityParent/guardian and participant (where aged ≥8 years) perception of facial nerve recovery at 1, 3 and 6 months using a lay translation of the HB scaleEmotional and functional wellbeing of the participant assessed by the parent/guardian and participant using the Pediatric Quality of Life Inventory (PedsQL) [39] and Child Health Utility 9D (CHU9D)scales [40–43] and sections of the Harter scale at 1,3, and 6 months [44].Pain at 1, 3 and 6 months assessed using child assigned visual analogue scale or Faces Pain Scale Revised (for participants aged 5 and older) and using a parent assigned visual analogue scale (VAS) [45–47]. Both pain scales are numbered 0–10.Prevalence of synkinesis or autonomic dysfunction at 1, 3 and 6 months using the Sunnybrook scale augmented by a synkinesis assessment questionnaire (SAQ) [48]Health utilization costs assessed via CHUD9 and via capture of information from the parent/guardian/participant related to in-patient, out-patient, or ED visits and to any other health facilities including general practitioner attendance for treatment or investigation during the 6 months following randomization.For patients not recovered at 6 months, recovery at 12 months as perceived by parents/guardian and participant (where aged ≥8 years) using a lay translation of the HB scale.

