### Study procedures

An overview and the timing of the study procedures are outlined in detail in Table 2.

**Table 2 Tab2:** Assessment Schedule BellPIC Study

Procedure	Enrolment & Randomisation Time point 1	Time point 2	Time point 3	Time point 4	Time point 5	Time point 6
	Day 1	Day 14^a^	Month 1^b^	Month 3^b^	Month 6^b^	Month 12^d^
Obtain Informed consent	✓					
Collect demographic and relevant information	✓					
Facial images	✓		✓	✓	✓	
House Brackmann [18, 27] & Sunnybrook [32, 38] scales augmented with SAQ [48]	✓		✓	✓	✓	
Review inclusion & exclusion criteria	✓					
Randomise	✓					
Study drug dispense	✓					
Study drug compliance review		✓	✓			
Adverse events review		✓	✓^e^			
Specialist clinician review			✓^c^			
Emotional and functional impact using PedsQL, CHU-9D and Harter scales [39–44]			✓	✓	✓	
Assessment of pain (VAS/FPS-R) [45–47]			✓	✓	✓	
Participant and parent perception of recovery (lay translation of HB scale)		✓	✓	✓	✓	✓
Collection of information on medical attendances			✓	✓	✓	

*HB* House Brackmann scale, *SAQ* Synkinesis Assessment Questionnaire, *PedsQL* Pediatric Quality of Life inventory, *CHU-9D* Child Health Utility 9D, *VAS* Visual Analogue Scale, *FPS-R* Faces Pain Scale Revised

^a^This assessment will be conducted over the telephone or on-line. A window of ±5 days is allowed

^b^A window of ± 7 days will be allowed to facilitate appointment scheduling for the study assessments attended on-site at 1 month; a window of ±14 days will be allowed to facilitate appointment scheduling or follow up contacts by phone, email or online for study visits or contacts at 3 and 6 months. Once a participant has been assessed to have made a complete recovery (HB score of 1), they will no longer be required to attend further visits to the study clinic and will only be required to complete questionnaires and scales by telephone, email or online at 3 and 6 months

^c^The senior specialist clinician may be a pediatric neurologist; ENT specialist; pediatrician; or ED physician

^d^This assessment will be required only for those deemed to have been not recovered at their 6 month assessment. A window of ±14 days will be allowed to facilitate follow up contacts scheduling

^e^Adverse events which are unresolved at 1 month should be followed till resolution or stabilisation

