#### Follow up assessment at 12 months

For participants not recovered at 6 months, a further contact will be conducted with the parent/guardian or participant with a request to complete a questionnaire on-line or by phone to elicit information on parent perceived recovery of Bell’s palsy. While this data point is outside the RCT period of 6 months, this will allow the determination of the 12 month recovery rate for Bell’s palsy in children which is unknown at this time.

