### Statistical methods

#### Sample size estimation

Based on observational data [4, 14] we expect 60 % of children without prednisolone to have complete recovery at 1 month. This is in line with data from the pediatric RCT which reported complete recovery without prednisolone in 72 % at 4 months [12]. A study in adults [18] deemed an improvement of 12 % with prednisolone compared with placebo to be a clinically important difference between treatment groups. We therefore power our study to find an increase in the proportion with complete recovery from 60 % in the placebo group to 72 % in the prednisolone group. This is a conservative estimate of efficacy compared with that found in our observational pilot data [4, 14] which showed an increase in complete recovery at 1 month of 16 % in those treated with prednisolone (75 %) compared with those not receiving prednisolone (59 %). To enable us to identify an increase in recovery from 60 to 72 % or larger with 80 % power requires a study with 244 subjects in each treatment group based on a two-sided test with α = 0.05. Hence we aim to recruit 270 per group (540 in total) to allow for 10 % loss to follow-up at 1 month.

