#### Statistical analysis

Data will be analysed on an intention-to-treat basis. For the primary analysis, multiple imputation will be used to handle missing data, imputing all outcomes using a single (joint) imputation model. Imputation will be carried out separately by treatment arm to ensure that any treatment effects are maintained. As a secondary analysis, all analyses will be repeated using a complete case analysis, including all participants with data available for each outcome.

The primary outcome of complete recovery at 1 month post randomization on the HB scale (as determined by the site specialist clinician) will be presented as a proportion in each treatment group, with a comparison between the groups presented as a difference in proportions and as an odds ratio from a logistic regression model adjusted for site and age, with a 95 % CI and *p*-value. In addition, we will present the results as Number-Needed-to-Treat (NNT) and its 95 % CI. As an additional sensitivity analysis, the analysis of recovery at 1 month will be repeated assuming that all participants with missing data who have not previously been recorded as achieving complete recovery 1) have recovered, and 2) have not recovered.

All secondary outcomes will be summarized by treatment group. Binary outcomes will be presented as proportions, with comparisons between the groups presented as a difference in proportions and as odds ratios from logistic regression adjusted for site, with 95 % CIs and *p*-values. Continuous outcomes will be presented as means and standard deviations, with comparisons made using linear regression adjusted for site presented as mean differences, 95 % CIs and *p*-values. Time to recovery will be assessed using a Cox proportional hazards model censoring patients who have not recovered at 6 months, with results presented as a hazard ratio, and its 95 % CI and *p*-value. Participants who have reached complete recovery at 1 or 3 months and are not assessed at the later time points will be assumed to have complete recovery for the duration of the study. For both the primary and secondary outcome, we will repeat the analysis adjusted for age (as a continuous variable), gender, baseline severity of facial nerve dysfunction (severe = HB V and VI, non severe = HB I-IV [18, [36]) and time to treatment (≥24 vs >24–72 hours [18, [36]) as potentially important confounders.

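### The 12-month recovery outcome is restricted to children unrecovered at 6 months, yet the analysis text compares it between arms as if the groups were still randomised

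*Protocol article*

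**What the plan says.** The Secondary outcomes section of the protocol article ends with this item: "For patients not recovered at 6 months, recovery at 12 months as perceived by parents/guardian and participant", measured on a lay translation of the House-Brackmann (HB) scale. Footnote d to Table 2 (Study procedures) limits data collection in the same way: "This assessment will be required only for those deemed to have been not recovered at their 6 month assessment".

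The Statistical analysis section then states: "All secondary outcomes will be summarized by treatment group. Binary outcomes will be presented as proportions, with comparisons between the groups". The comparison is a difference in proportions and a site-adjusted odds ratio, with confidence intervals and p-values. No secondary outcome is exempted. The same section carries recovery forward for children who recovered at 1 or 3 months and were not assessed later. It does not mention children first recovered at 6 months.

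The section on follow-up at 12 months places this data point outside the 6-month trial period and gives its purpose: "this will allow the determination of the 12 month recovery rate for" Bell's palsy in children. It does not say whether the arms will be compared.

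**The concern.** Randomisation makes the arms comparable as wholes. It does not do so for subgroups picked out by something that happens after treatment starts. Being unrecovered at 6 months is such an event, and recovery at 6 months is itself a listed efficacy outcome. If prednisolone brings some slower children to recovery before month 6, they leave the prednisolone denominator while their counterparts stay in the placebo denominator. The prednisolone group at month 12 would then hold a larger share of children who would not recover in either arm.

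A reader given the resulting odds ratio and p-value could take an effect of selection for an effect of treatment. If no child on one arm were unrecovered at 6 months, the comparison would not exist.

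**Working it through.** **The plan's own figure.** The only sample size stated is for the 1-month primary outcome: "244 subjects in each treatment group", from a "two-sided test with α = 0.05", 80% power, and an increase "from 60 % in the placebo group to 72 % in the prednisolone group". With pooled variance, n = [1.960 × √(2 × 0.66 × 0.34) + 0.842 × √(0.60 × 0.40 + 0.72 × 0.28)]² / 0.12² = (1.313 + 0.560)² / 0.0144, which rounds up to 244. It reproduces. It does not bear on the 12-month outcome, for which the article gives no size or power.

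**How many children would be asked.** The Background section cites a paediatric randomised trial with 6-month recovery of 100% with steroid and 85% without. With 270 per arm, 0.15 × 270 = 40.5 placebo children would be unrecovered. With 10% lost, 0.15 × 243 = 36. If prednisolone reached the cited 100%, its denominator would be zero.

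**Bias when treatment only changes timing.** The article gives no planning value for recovery between 6 and 12 months, so what follows is assumed. Let u be the placebo proportion unrecovered at 6 months, q the share of those who recover by 12 months, and f the share of u that prednisolone moves to recovery by 6 months, all drawn from late recoverers (f no larger than q). Then:

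- restricted rate, placebo: q
- restricted rate, prednisolone: (q − f) / (1 − f)
- recovered by 12 months among all randomised, both arms: 1 − u(1 − q)

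With u = 0.15 and 270 per arm:

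| q | f | Prednisolone, restricted | Difference (points) | Children asked, placebo / prednisolone | All randomised, each arm |
|---|---|---|---|---|---|
| 0.80 | 0.25 | 0.55/0.75 = 73% | −7 | 40.5 / 30.4 | 97.0% |
| 0.80 | 0.50 | 0.30/0.50 = 60% | −20 | 40.5 / 20.3 | 97.0% |
| 0.80 | 0.75 | 0.05/0.25 = 20% | −60 | 40.5 / 10.1 | 97.0% |
| 0.50 | 0.25 | 0.25/0.75 = 33% | −17 | 40.5 / 30.4 | 92.5% |
| 0.50 | 0.50 | 0/0.50 = 0% | −50 | 40.5 / 20.3 | 92.5% |

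The restricted rates do not depend on u. If placebo recovery at 6 months were 90% or 95%, the same percentages would rest on 27 or 13.5 placebo children.

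**A case with true benefit.** Assume placebo children split 85% recovered by 6 months, 10% later and 5% never, and prednisolone children 93%, 3% and 4%. Among all randomised, recovery by 12 months is 96% on prednisolone against 95% on placebo. The restricted comparison is 0.03/0.07 = 43% against 0.10/0.15 = 67%, which is −24 points. The sign is reversed.

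**When nothing goes wrong.** If f = 0, both restricted rates equal q. If q = 1, the prednisolone rate is (1 − f)/(1 − f) = 1 and both arms are at 100%. Drawing all accelerated children from late recoverers is also the least favourable assumption. If they came in equal proportion from late recoverers and children who never recover, the restricted rates would be equal.

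**The case against.** The strongest reply is that the 12-month contact was never meant as an efficacy comparison. The section that describes it puts it outside the trial period and gives it a natural-history purpose. The Cox model censors at 6 months, the interaction analyses stop at 6 months, and so does the economic evaluation. The comparison arises only from a general sentence covering a long list of outcomes. This shows the intent was probably descriptive, and it limits the weight of the point. It does not remove it: the item is listed as a secondary outcome, the analysis text covers all of them, and nothing says this one will not be tested.

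A reader might infer that an effective drug would look harmful here. The documents do not support that. Bias needs an effect by 6 months and some children still unrecovered at 12 months, and the cited paediatric trial reported full recovery by 12 months in both groups. Its relevance is limited: it had 42 children, and the Primary outcome section indicates it counted HB grade 1 or 2 as recovered, whereas this trial requires grade 1. Small numbers also blunt any false signal. An assumed 12/24 against 24/36 is −17 points with standard error √(0.25/24 + 0.222/36) = 0.129, so a 95% interval of about −42 to +9.

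A reader might also infer that the 12-month recovery rate cannot be obtained, or must mix clinician and lay grading. Neither follows. Children recovered by 6 months plus the later answers of the rest largely give the rate, and Table 2 schedules the lay HB scale for everyone at month 6. What is missing is the rule for children first recovered at 6 months and a statement of which scale applies. How missed visits are handled may be set out in the full protocol, which is not shown.

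**Conclusion.** The point holds as a conditional one. As written, the plan applies a between-arm test to a group selected by a post-randomisation result that treatment is meant to affect. If prednisolone changes recovery by 6 months, that comparison loses the protection of randomisation. It could be biased against prednisolone, or could not be estimated if one arm is empty.

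The illustrated differences, −7 to −60 points with no true 12-month difference, rest on assumed splits between late recovery and no recovery, on 85% untreated recovery at 6 months from a small trial with a wider definition, and on 270 children per arm. They show what is possible and are not a forecast. The primary outcome and the recovery outcomes at 1, 3 and 6 months are untouched. The correction is still worth making because it is specific and nearly free.

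**What to change.** 1. For any between-arm comparison, define the outcome as recovered by 12 months among all randomised children.
2. Extend the carry-forward rule in the Statistical analysis section to children first recovered at 6 months.
3. State one scale for the outcome. If it is the lay HB scale, amend footnote d so that the month-12 contact goes to every child not recovered on that scale, or without a recorded recovery at the last completed assessment. Otherwise a child graded recovered by the clinician but not on the lay scale would have no 12-month data.
4. Report the 12-month rate among children unrecovered at 6 months descriptively by arm, with no odds ratio or p-value.

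The cost is rewording the outcome, footnote d and the carry-forward rule, plus a few more online or phone contacts. No new visit or instrument is needed.
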